#### Secondary outcomes.

Pain description – Free narrative reportNumber of analgesics taken – Paracetamol intake recorded from baseline to 48 hours after T 380 copper IUD placement.Anxiety – Assessed using the Generalized Anxiety Disorder 7 (GAD-7) questionnaire [15] 15 minutes after IUD placement.Quality of life – Measured using the WHOQOL-Pain instrument [16] from baseline to 48 hours after placement.Patient satisfaction – Assessed through close-ended questions [6] 15 minutes after placement.Time required for relief of abdominal discomfort (menstrual cramps) – Measured in days from baseline.Verification of successful placement – Investigated dichotomously (success/failure) from baseline to 48 hours after placement.Adverse effects – Including uterine perforation, IUD displacement, abdominal pain, increased vaginal bleeding, and allergic reactions. An open-ended question will be used for the participants to report adverse effects, followed by a list of potential impacts to help them recall any unreported symptoms.Side effects – including cramps, mild pain, light bleeding, and tongue numbness. An open-ended question will be asked first, followed by a list of potential side effects to improve recall.

*Primary outcome – Pain - Visual Analog Scale (VAS)*: Pain will be assessed using the Visual Analog Scale (VAS), as illustrated below. One end of the scale is marked “0”, corresponding to the absence of pain, and the other end is marked “10”, indicating unbearable pain. The same scale will be used for all participants. The same operator will always provide instructions for marking the scale. Pain scores will be recorded, and this assessment will be performed at all study visits, including during the IUD insertion phases (Pozzi, hysterometry, and IUD placement), at 5 and 15 minutes after placement, and at 24 and 48 hours after the procedure. The participants will be asked about spontaneous pain at three distinct moments during placement: pain during clamping with the Pozzi forceps, pain during hysterometry (uterine length measurement), and pain during the actual IUD placement. All participants will receive daily phone call reminders to ensure accurate recording of their outcomes [17].

Cervical clamping: Gently clamp the anterior lip of the cervix using Pozzi forceps to stabilize it during placement.Hysterometry: Slowly and carefully insert the hysterometer to determine uterine depth and angulation, minimizing the risk of uterine perforation.Placement of IUD in the uterine cavity

*Secondary outcome – Description of pain – Free Narrative*: Immediately after IUD placement, the patients will be asked to describe their experience with the procedure. The responses will be recorded verbatim to enable qualitative analysis.

*Secondary outcome – Quantity of analgesics (amount taken by the patient will be recorded at 24 and 48 h after the T 380 copper IUD placement*: Analgesic (paracetamol) consumption will be assessed as proposed by Bauer et al. (2013; [18]). At the beginning of the study, each participant will receive a blister pack of paracetamol, which is a pure analgesic [19]. The blister pack must be kept until the end of the study, and the analgesic will be used only for pain. At the end of the study, the number of remaining tablets will be quantified as an additional measure of pain. The analgesic will be paracetamol 500 mg to be taken only when necessary at a dosage of one tablet every six hours. The participants will be asked to record in writing the number of tablets taken, along with the date and time of consumption. A monitoring procedure will be implemented to ensure adherence: the participants will be required to bring their blister pack to follow-up visits for verification. Medication use will be tracked from baseline through 48 hours post-placement.

*Secondary outcome – Anxiety assessment*: Anxiety levels in patients undergoing T 380 copper IUD placement for contraception will be assessed using the seven-item Generalized Anxiety Disorder (GAD-7) questionnaire administered at baseline and 15 minutes after the procedure [15]. The GAD-7 is a self-report instrument designed to assess generalized anxiety symptoms based on the DSM-IV diagnostic criteria. The questionnaire consists of seven items measuring the frequency of anxiety-related issues over the previous two weeks, using a 4-point Likert scale: 0 = Never, 1 = Several days, 2 = More than half the days, 3 = Almost every day. The GAD-7 can be administered in clinical and research settings, both in person and online, and takes approximately five minutes to complete. The total score ranges from 0 to 21 points, with higher scores indicating greater severity of anxiety symptoms. Classification is divided into four categories: scores from 0 to 4 indicate no anxiety, 5–9 correspond to mild anxiety, 10–14 correspond to moderate anxiety, and 15–21 indicate severe anxiety. The GAD-7 has strong validity and reliability and is widely used in clinical and non-clinical populations. Depending on the application context, it can be analyzed using a unifactorial or bifactorial model (somatic and cognitive-emotional items).

*Secondary outcome – Assessment of quality of life using the WHOQOL-Pain instrument at baseline and 24 hours after the procedure*: The WHOQOL-Pain is an additional module of the WHOQOL-100 specifically developed to assess quality of life in individuals living with chronic pain. Following a preliminary study, ten new facets related to pain and discomfort were identified, four of which were selected for the final version of the instrument: Pain Relief; Anger and Frustration; Vulnerability, Fear and Concern; and Uncertainty [16]. Each facet comprises four questions that address different dimensions of the pain experience. The responses are recorded on a five-point Likert scale to measure intensity, capacity, evaluation, and frequency. The scores are converted to a 0–100 scale, enabling the quantitative interpretation of pain levels and the impact on quality of life. The WHOQOL-Pain items are not integrated into the WHOQOL-100 and are applied separately at the end of the main questionnaire. This structure facilitates the individualized analysis of pain-related facets, enabling a specific, detailed assessment of physical chronic pain experiences.

Patient satisfaction with T 380 copper IUD placement for contraception will be assessed 15 minutes after the procedure using guiding questions [6]. The assessment will include whether the placement experience was unpleasant, whether the patient would undergo the procedure again, and whether she would recommend it to a friend.

*Secondary outcome – Time required to relieve abdominal discomfort following PBM*: The time required to relieve abdominal discomfort following PBM will be recorded in hours, measured from the onset of cramps until complete pain resolution.

*Secondary outcome – Verification for IUD placement success*: IUD placement will be assessed as a binary outcome (success/failure).

*Secondary outcome – Adverse effects (uterine perforation, IUD displacement, abdominal pain, increased vaginal bleeding, and allergy)*: An open-ended question will be asked to elicit the patient’s free responses regarding adverse effects. The responses will then be listed nominally so that the patient may recall any impact that she may have forgotten to report.

*Secondary outcome – Side effects (cramps, mild pain, mild bleeding, tongue anesthesia)*: An open-ended question will be asked to enable the patient to freely describe any side effects. Effects will then be listed by name to help the patient recall any impact that she may have forgotten to report.

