### IUD placement protocol according to the recommendations of the ministry of health

Before the procedure, the steps will be explained to the patient again to reduce anxiety and promote relaxation during IUD placement. A two-hand pelvic examination will be performed to assess the size, position, and mobility of the uterus. Infection prevention measures will be implemented, including the use of sterile gloves and cervical cleansing with a chlorhexidine-based antiseptic. The anterior lip of the cervix will be gently grasped with Pozzi forceps to ensure stabilization during placement. A hysterometer will be introduced slowly and carefully to determine uterine depth and angulation, thus minimizing the risk of perforation. During IUD preparation, all instruments and gloves will be maintained sterile, and the device will be assembled according to the manufacturer’s instructions, with the arms kept horizontal during insertion. The retractable technique will be used for placement. The insertion tube will be advanced to the uterine fundus. The tube will then be partially withdrawn while keeping the plunger fixed, thereby releasing the arms of the IUD. After a few seconds, the plunger and insertion tube will be removed. The IUD strings will be trimmed to 2–3 cm from the cervix. The patient will remain lying down for approximately 15 minutes to reduce discomfort. Following placement, the patient will be monitored for well-being and possible vasovagal reactions (e.g., sweating, nausea, or fainting), which are rare and self-limiting. The length of the IUD strings relative to the cervix will be documented in the medical record. The patient will be instructed to return for a follow-up visit in 30 days to verify IUD positioning and adaptation.

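### IUD displacement is collected only by asking the woman, with no stated window, while the one visit described as checking device position, at 30 days, feeds no listed outcome

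*Protocol article*

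**What the plan says.** All places are in the protocol article.

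- **Placement success.** The list under Secondary outcomes has verification of successful placement, "Investigated dichotomously (success/failure) from baseline to 48 hours after placement". The fuller description later in that section adds only that the outcome is binary.
- **Displacement.** The same list gives adverse effects as "Including uterine perforation, IUD displacement, abdominal pain, increased vaginal bleeding, and allergic reactions". On method, the fuller description says "An open-ended question will be asked to elicit the patient’s free responses regarding adverse effects". A list of possible effects is then read to aid recall. Neither place gives a time window.
- **Position check.** The section on the IUD placement protocol says "The patient will be instructed to return for a follow-up visit in 30 days to verify IUD positioning and adaptation". It also says "The length of the IUD strings relative to the cervix will be documented in the medical record".
- **Other contacts.** Pain is recorded during insertion, then "at 5 and 15 minutes after placement, and at 24 and 48 hours after the procedure", with daily phone reminders. Pain assessment is also said to take place at all study visits. For paracetamol counts, "the participants will be required to bring their blister pack to follow-up visits for verification". These visits carry no dates and are not described as including an examination of the device.

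**The concern.** Displacement is a finding about where the device lies. A woman may have no symptom that tells her it has moved, so a question and a recall list are a weak instrument for it. The text does describe a visit meant to verify position, but no listed outcome is connected to that visit.

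A site following the text could therefore record no displacement in either arm because position was never examined for the purpose of the outcome. A reader of the results would naturally take that as reassurance about device safety under PBM. The article already says that the study poses no risk and that no adverse events are expected with PBM, so an empty displacement row would probably be read that way.

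The 48-hour window on placement success adds to the confusion. It suggests a status that is followed after insertion, yet no check of such a status is described inside those 48 hours.

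**Working it through.** The plan gives no figure to reproduce on this point. The check sets the passages side by side, and a short illustration shows the scale.

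**1. Outcome, source and timing**

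| Item | How it is obtained | When |
|---|---|---|
| Placement success | Binary; no criterion given | Baseline to 48 hours |
| IUD displacement | Participant's answers: open question, then list | No window stated |
| String length relative to the cervix | Medical record | In connection with placement |
| Position verification | Return visit | 30 days; tied to no listed outcome |

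**2. Placement success.** If success means that the device was inserted and released, the operator knows the answer when the procedure ends. The outcome is then observable, and running the window to 48 hours adds no information. If it means that the device stays in position, the window would matter, but no check of position within it is described. The article does not say which meaning applies. On either meaning the window needs changing or explaining.

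**3. Displacement.** The stated source is the participant. The string length recorded around placement could serve as a reference for a later examination, but the text does not link it to an outcome. The undated follow-up visits are described for pill counts. That leaves the 30-day visit as the only described source of an examined position.

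**4. Scale, on assumed rates.** Let p be the true proportion displaced by day 30 and s the share of those women who notice and report it. The documents give neither. With 72 women, the expected number truly displaced is 72 × p:

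- p = 1%: 72 × 0.01 = 0.72
- p = 2%: 72 × 0.02 = 1.44
- p = 5%: 72 × 0.05 = 3.6
- p = 10%: 72 × 0.10 = 7.2

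The expected number recorded is 72 × p × s, and the chance that none is recorded is (1 − p × s)^72. At p = 5%:

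| s | Expected number recorded | Chance of recording none |
|---|---|---|
| 1 (every case found) | 3.6 | 0.95^72 = 0.025 |
| 0.5 | 1.8 | 0.975^72 = 0.16 |
| 0.25 | 0.9 | 0.9875^72 = 0.40 |
| 0 | 0 | 1 |

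If every case is found, an empty row is real evidence against a 5% rate. If only a quarter are reported, an empty row is quite likely even when 5% are displaced. The stated method leaves s unknown.

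**5. What a better source can show.** With 36 women per arm, a 6–0 split gives a two-sided Fisher p of 2 × C(36,6)/C(72,6) = 2 × 1,947,792/156,238,908 = 0.025. A 5–0 split gives 2 × C(36,5)/C(72,5) = 2 × 376,992/13,991,544 = 0.054. With this few events, the outcome is descriptive even when ascertained well.

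**The case against.** The strongest case against is that the two sections do not contradict each other. One describes placement under Ministry of Health recommendations, including a return visit; the other lists trial outcomes. A care visit that no outcome uses is not in itself an error. The schedule figure, the flowchart and the full protocol are not shown, so success criteria and visit timing may be settled there. The trial concerns pain over 48 hours, and a day-30 comparison would have little power.

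Much of this stands, and it rules out several stronger readings that a reader might infer:

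- **That placement success cannot be observed.** The documents do not support this. The operator can score insertion at the procedure, and the same investigator performs placement and post-procedural assessment.
- **That displacement is closed at 48 hours.** That limit is written beside placement success, not beside adverse effects. The displacement window is undefined, and nothing bars recording a displacement found at day 30.
- **That phone calls and self-recorded scales are the only contacts before day 30.** Undated study and follow-up visits are mentioned, so this cannot be asserted.
- **That bleeding is followed for too short a time.** The documents give no time course for bleeding, so there is no basis for this.

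What the objection does not remove is the method that the article does state. Displacement is collected by self-report, which suits symptoms and not device position, while a scheduled visit meant to verify position goes unused. That concerns what is written, not detail left to another document. Low power argues for descriptive reporting, not for leaving the event unexamined.

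**Conclusion.** The point holds in a limited form. Insertion success is observable, but its 48-hour window serves no purpose. Displacement without symptoms would be missed by the stated method, and its window is not defined. A finding of no displacement in both arms would not rest on any described examination.

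This affects the displacement row of the adverse effects and the wording of one other secondary outcome. It does not touch the primary pain outcome or the sample size. The number of missed events cannot be derived from the documents. The assumed rates of 1% to 10% imply 0.7 to 7.2 affected women of 72, and the share who would report it is unknown. The conclusion does not depend on those rates. It rests on reading the article as written; the full protocol could already link the 30-day visit to the outcomes, in which case the article should say so.

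**What to change.** 1. Define insertion success and score it at the end of the procedure, counting failed attempts. Drop the 48-hour window from this outcome.
2. Take displacement or expulsion from the position check at the 30-day visit already described, recorded by staff blinded to arm. Report it by arm as a descriptive safety outcome.
3. State the adverse-effect window so that it includes that visit, and keep the open question and list for effects that participants can feel.
4. If the 30-day visit is routine care outside the trial, say so and make no claim about displacement.

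This takes protocol wording and one form at an existing visit; no procedure is added. Some women will miss day 30, so numbers examined should be reported by arm. Data lock moves from 48 hours to 30 days after the last insertion, 30 − 2 = 28 days or about four weeks later. With few events expected, the comparison between arms stays descriptive.

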### Inclusion and exclusion criteria

The study will include women aged 18–50, with no restrictions on race or socioeconomic status. Both nulliparous and multiparous women will be considered eligible, provided they meet other criteria established to ensure the safety and appropriateness of the IUD placement procedure.

Conversely, women with suspected or confirmed pregnancy, a history of diagnosed chronic pain, or active pelvic infection will be excluded from the study. Women who took pain medication within 12 hours before the procedure will be excluded to prevent interference with pain perception. Women with known contraindications for IUD placement, such as significant uterine cavity distortion, active pelvic inflammatory disease, or Wilson’s disease, will be deemed ineligible [4]. Other exclusion criteria include copper allergy, unexplained abnormal uterine bleeding [4], a history of photosensitivity, or any condition affecting the lumbar region, such as active neoplasms, established osteomyelitis, or pre-existing deep tissue injuries with necrosis or infection. The participants will not be permitted to participate in any other clinical study during the trial.

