### Statistical analysis

Statistical analysis will be performed using the Statistical Package for the Social Sciences (SPSS) version 24.0 or equivalent software package. The significance level will be set at 5% (p < 0.05) for all tests. Data normality will be determined using the Shapiro-Wilk test. Continuous variables will be reported as either the mean and standard deviation or the median and interquartile range, depending on the distribution of the data. Categorical variables will be expressed as absolute and relative frequencies. For comparisons between the experimental group (active PBM) and control group (sham PBM), the Mann-Whitney test will be used for continuous variables with non-normal distribution. When the expected minimum value is less than 5, categorical variables will be compared using either the chi-square test or Fisher’s exact test. The analysis of pain-related variables (intensity measured by the Visual Analog Scale [VAS]) at different time points (baseline, during placement, 5 and 15 minutes, and 24 hours after the procedure) will be conducted using the Friedman test. As the primary outcome will be measured repeatedly over time, the analysis will account for the within-subject correlation inherent to this repeated-measures design.

For the measures of anxiety (GAD-7), quality of life (WHOQOL-100), and satisfaction with the procedure, the Mann-Whitney test will be used to compare groups across assessment time points. The use of post-procedural analgesics will be compared between groups using repeated-measures analysis of variance (ANOVA). No interim analyses or stopping guidelines are planned due to the short duration of the trial and low risk.

Missing data will be assessed for frequency and pattern. In the event of missing values, the analyses will be performed using the available data, and the extent of missingness will be reported. If necessary, appropriate statistical methods will be applied depending on the nature and proportion of the missing data.

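### The GAD-7, a two-week recall scale, is given 15 minutes after insertion; it cannot register anxiety during or just after the procedure, so a null anxiety result would be uninterpretable

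*Protocol article*

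**What the plan says.** **Anxiety.** The detailed description under Secondary outcomes has the GAD-7 "administered at baseline and 15 minutes after the procedure". It then explains the scale: "The questionnaire consists of seven items measuring the frequency of anxiety-related issues over the previous two weeks". The four answers run from never, through several days and more than half the days, to almost every day. The short outcome list in the same section gives the GAD-7 at 15 minutes only and mentions no baseline.

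**Quality of life.** The detailed description introduces WHOQOL-Pain as a module "specifically developed to assess quality of life in individuals living with chronic pain". The eligibility section excludes women with "a history of diagnosed chronic pain". The detailed description assesses quality of life "using the WHOQOL-Pain instrument at baseline and 24 hours after the procedure", while the outcome list says "from baseline to 48 hours after placement".

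**Analysis.** The Statistical analysis section states: "For the measures of anxiety (GAD-7), quality of life (WHOQOL-100), and satisfaction with the procedure, the Mann-Whitney test will be used to compare groups". The sentence goes on to refer to the assessment times, but it names no covariate and no change score. The same section says: "The significance level will be set at 5% (p < 0.05) for all tests".

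**The concern.** The Abstract and Introduction give fear and anticipatory discomfort as reasons for the trial, so readers will look to the anxiety outcome for an answer. A scale that counts symptomatic days over a fortnight describes a woman's recent general state. It does not describe what she feels on the examination couch. If the arms do not differ on it, one cannot tell whether PBM leaves procedural anxiety unchanged or the scale could not show a change. Such a result could still be published as no benefit on anxiety, and the missing measurement cannot be recovered afterwards.

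The quality-of-life outcome raises smaller questions: whether the module suits these women, which instrument and follow-up time are meant, and whether the baseline score is put to use.

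**Working it through.** **1. No planned figure to reproduce.** The sample size of 72 (36 per arm) is derived for repeated VAS pain measurements. The protocol gives no effect size or power for anxiety or quality of life.

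**2. What the 15-minute GAD-7 can contain.** The recall window is the 14 days before the reading. PBM belongs to the procedure visit, so almost all of the window precedes any effect it could have.
- If baseline is taken on the same day, both readings cover nearly the same fortnight.
- If baseline is earlier, the windows differ, but the days by which they differ also precede treatment.

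The argument therefore does not depend on the baseline date, which the text does not give. Moving an item from never to the next answer requires several symptomatic days, and one short episode does not supply them.

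**3. What this means for power (illustration only).** Approximate power of a two-sided 5% Mann-Whitney test is Φ(d·√(n/2) − 1.96). Here n = 36 × 0.955 = 34.4 per arm (0.955 is the test's efficiency against the t-test under normality) and √(34.4/2) = 4.15. Assume a true effect on momentary anxiety of d = 0.8, of which the scale captures a share s:

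| s | s × 0.8 | Power |
|---|---|---|
| 1 | 0.8 | 91% |
| 1/2 | 0.4 | 38% |
| 1/4 | 0.2 | 13% |
| 0 | 0 | 5% (the test level) |

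Both d and s are assumptions. Literal answering puts s at or near 0. The document does not allow s to be estimated.

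**4. Baseline adjustment for quality of life.** With 36 per arm, a Mann-Whitney test on follow-up scores alone has 80% power at d of about 0.69 (noncentral t, same efficiency; 0.686 before rounding). Adjusting for a baseline that correlates r with follow-up multiplies this by √(1 − r²):
- r = 0.5: 0.686 × 0.866 = 0.59
- r = 0.7: 0.686 × 0.714 = 0.49
- r = 0.9: 0.686 × 0.436 = 0.30

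The correlations are assumed. The calculation carries the same efficiency over to rank-based adjustment.

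**5. Statements that disagree.**

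| Item | One place | Another place |
|---|---|---|
| Quality-of-life instrument | WHOQOL-Pain: Calibration/Training; Secondary outcomes (list and description) | WHOQOL-100: Abstract; Statistical analysis |
| Quality-of-life follow-up | 24 hours: description | Up to 48 hours: list |
| GAD-7 | 15 minutes only: list | Baseline and 15 minutes: description |

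**The case against.** Several points on the other side are sound.

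- **Respondents do not always answer literally.** A woman's present mood may colour her account of the fortnight, so the arms could differ on the GAD-7. That makes a difference possible but does not make it a measure of procedural anxiety.
- **Quality of life.** A reader might infer that WHOQOL-Pain, too, can barely detect an effect. The document does not support that. It states no recall period for the module, the follow-up is at least 24 hours later, and facets on pain relief and on fear could respond. Use outside the population for which the module was built questions its validity but does not prove it insensitive.
- **Unadjusted test.** A reader might infer that arm differences would only reflect baseline imbalance, or that the comparison is biased. Under 1:1 randomisation the Mann-Whitney test is valid and only precision is lost. The reference to assessment times also leaves room for some use of baseline, and an analysis plan that is not shown may say more.
- **The recall ratio.** Fifteen minutes is 15/(14 × 24 × 60) = 15/20,160, or 0.07% of the window. The arithmetic is right, but the scale is scored in categories of days, so the ratio measures neither bias nor loss of power.
- **Instrument name.** The protocol presents WHOQOL-Pain as an add-on to the WHOQOL-100, so the other name may simply refer to the parent questionnaire. Since the module's items are scored apart from the parent, the text still has to say which score is analysed.

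None of these answers the GAD-7 point, which rests on the protocol's own account of the scale.

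**Conclusion.** The point holds for the GAD-7. As described and timed in the protocol, it cannot register anxiety during or just after insertion, and a null result on it would say nothing about PBM. The only assumption is that women answer the items as worded. The loss of power in practice cannot be quantified from the document, and the table of shares is illustrative.

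For quality of life the conclusion is weaker. Insensitivity is possible but not shown, and the chronic-pain target population is reason enough to read the result as exploratory. Baseline adjustment would lower the detectable effect from about 0.69 to between 0.59 and 0.30 SD for assumed correlations of 0.5 to 0.9. It would improve precision without correcting any bias. The disagreements on instrument, follow-up time and GAD-7 timing are real and need only reconciling.

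The outcomes concerned are secondary, and the primary VAS analysis is not touched. The change should be made, but the trial's main question does not depend on it.

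**What to change.** 1. **Anxiety.** Keep the GAD-7 at baseline only, to describe the sample. Measure anxiety by one 0-10 rating of how anxious the woman feels right now, at baseline (before the envelope is opened) and at 15 minutes. Compare arms by ANCOVA of the 15-minute rating on the baseline rating, rank-based if skewed. It is tempting to enter the baseline GAD-7 as a covariate for VAS pain as well, but the Friedman test named for that outcome takes no covariate.
2. **Quality of life.** Compare follow-up scores adjusted for the baseline score in the same way, and label WHOQOL-Pain exploratory.
3. **Wording.** State one quality-of-life instrument, one follow-up time and one GAD-7 schedule in the Abstract, Calibration/Training, Secondary outcomes and Statistical analysis.

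**Cost.** One item replaces seven at 15 minutes, with no extra visit or participant. The anxiety change will no longer be on the GAD-7 scale, and the team will have to justify the single item. The change is an amendment, so the ethics committee and registry must be notified; the Ethical aspects section provides for this. The protocol lists the trial as not yet recruiting, so the change can still precede data collection if that status holds.

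### The GAD-7, which asks about the previous two weeks, is poorly suited as a between-arm anxiety outcome 15 minutes after the procedure

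*Protocol article*

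**What the plan says.** All references are to the protocol article.

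- **Instrument (Secondary outcomes, Anxiety assessment).** The GAD-7 is "designed to assess generalized anxiety symptoms based on the DSM-IV diagnostic criteria". It has "seven items measuring the frequency of anxiety-related issues over the previous two weeks, using a 4-point Likert scale", with the options "0 = Never, 1 = Several days, 2 = More than half the days, 3 = Almost every day". On scoring: "The total score ranges from 0 to 21 points".
- **Timing, detailed text (same subsection).** It is "administered at baseline and 15 minutes after the procedure".
- **Timing, outcome list (Secondary outcomes).** Anxiety is "Assessed using the Generalized Anxiety Disorder 7 (GAD-7) questionnaire [15] 15 minutes after IUD placement". No baseline reading is listed there.
- **Analysis (Statistical analysis).** For anxiety, quality of life and satisfaction, "the Mann-Whitney test will be used to compare groups across assessment time points".
- **Start of treatment (Allocation).** The envelope is opened and the assigned PBM or sham is given immediately after placement. The study aim and the title of Table 1, however, call the PBM preventive.

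Nothing in the article shortens the recall period, rewords the items to the present moment, or adds a measure of state anxiety.

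**The concern.** The instrument and the time point do not fit together. A between-arm comparison after treatment is meant to show what the treatment did. This questionnaire asks about a fortnight that had almost entirely passed before treatment began, and it records the answers as counts of days. Relief or distress lasting minutes has no proper place on such a scale.

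What is at stake is the interpretation of one named outcome. The Abstract lists anxiety among the secondary outcomes, and the Introduction presents insertion pain as bearing on anticipatory fear, so readers will look for an anxiety result. If the arms do not differ, the result may be taken as evidence that PBM does not help anxiety around the procedure. If they do differ, it may be taken as evidence that it does. The measurement as planned supports neither reading. Once women have been treated, a missing state measure cannot be recovered for them.

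**Working it through.** The article gives no figure for this outcome that could be reproduced, beyond the score range: 7 items × 3 points = 21, as stated. The check is of how much of the recall window treatment could reach.

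**Inputs**
- Recall window: two weeks (Anxiety assessment) = 14 × 24 × 60 = 20,160 minutes, or 14 × 24 = 336 hours.
- Outcome reading: 15 minutes after the procedure (Anxiety assessment; outcome list).
- Start of treatment: right after placement (Allocation). Because the PBM is also called preventive, a second case is shown in which it starts about 60 minutes before the reading. The 60 minutes is an assumption.
- Gap between the baseline GAD-7 and the 15-minute GAD-7: not stated. A range is shown.

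**Step 1. Share of the outcome window that follows the start of treatment**

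Share = minutes from start of treatment to reading ÷ 20,160.

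- Start right after placement: 15 ÷ 20,160 = 0.00074, or 0.07%.
- Start about 60 minutes before the reading (assumption): 60 ÷ 20,160 = 0.0030, or 0.3%.

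This step does not depend on when, or whether, a baseline GAD-7 is taken.

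**Step 2. What the answer scale can register**

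The smallest step, from 0 to 1, requires symptoms on several days. The procedure day is one day in 14. A woman already at the border between two higher categories might be tipped by one more day, but most of that day's anxiety, including any while waiting and during insertion, can precede treatment. PBM given minutes before the reading does not undo a day on which the symptom had already occurred.

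**Step 3. Overlap of the baseline and outcome windows (conditional)**

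Overlap = 1 − gap in hours ÷ 336.

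| Gap between readings (assumed) | Overlap |
|---|---|
| 0.5 h | 99.9% |
| 1 h | 99.7% |
| 2 h | 99.4% |
| 1 day (24 h) | 92.9% |
| 7 days (168 h) | 50.0% |

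If both readings fall at the same visit, they cover almost the same fortnight. If baseline is taken a week earlier, half the window is new, but Step 1 still applies: nearly all of the new half also precedes treatment.

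**Step 4. The two timing statements side by side**

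The outcome list has one reading, at 15 minutes. The detailed subsection has two, at baseline and 15 minutes. The analysis text refers to time points without naming them, so it does not settle the matter.

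**The case against.** **The GAD-7 is self-reported, and people do not keep a strict ledger of days.** A woman asked 15 minutes after a painful procedure may let her present state colour her answers, so the score could move. This stands, and it limits the claim. A reader might infer that no effect could ever show, that power equals the 5% test level, or that a significant difference could only be chance imbalance. The article does not support these readings. The arithmetic concerns nominal recall time, not how women respond; no power can be derived from it; and state-coloured answers are a second route to a difference. Such a difference would still not be a valid score on the scale as described, and the severity bands in the article would not apply to it.

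**The date of the baseline reading is unknown.** This also stands. The schedule figure is not shown, and a reader might take near-complete overlap of the two windows as a fact of the design. It holds only if both readings are taken at the same visit. The main point does not need it.

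**The full protocol may use a modified form.** The supplementary files are not shown, so a changed recall instruction cannot be excluded. The article, however, describes the standard two-week form and no other.

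**The stated hypothesis concerns pain, and anxiety is one of several secondary outcomes.** This is correct, and it limits the weight of the point. Even so, a between-arm test on a post-treatment reading implies interest in a treatment effect.

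**The GAD-7 is described as valid and reliable.** That description belongs to an instrument aimed at generalized anxiety symptoms. It does not make the GAD-7 a measure of change over minutes.

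**Conclusion.** The concern holds in this form: the GAD-7 as described is poorly suited to a between-arm anxiety outcome at 15 minutes. At most about 0.07% of its recall window follows treatment under the Allocation section's timing, or about 0.3% under the assumed earlier start, and its answers count days. Answered as worded, it measures generalized anxiety from before treatment, so the planned comparison cannot be validly read as showing either an effect or the absence of one on anxiety around the procedure.

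This rests on the two-week wording being used as the article describes it. It does not rest on the timing of the baseline reading. The overlap of 99.4% to 99.9% is conditional on a gap of 0.5 to 2 hours.

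The conflict between the outcome list and the detailed subsection over a baseline GAD-7 is a separate, plain inconsistency that needs correcting.

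The point should be addressed before recruitment. It does not touch the primary pain outcome, its analysis or the sample size.

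**What to change.** 1. Give the GAD-7 once, at baseline, as a descriptor of the sample or a covariate.
2. Make the anxiety outcome a state measure, taken at baseline before the procedure and before any PBM or sham, and again at 15 minutes. One option is a 0–10 item on how anxious the woman feels right now, placed beside the pain VAS; another short state scale would also serve.
3. Compare the arms on the 15-minute state score adjusted for its baseline value, in place of the Mann-Whitney comparison of GAD-7 scores.
4. Align the Abstract, the outcome list, the Anxiety assessment subsection and Statistical analysis on instrument and time points. Also reconcile the statements on when PBM is given relative to placement, since they determine what a 15-minute reading can reflect.

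If the investigators prefer to keep the second GAD-7, the minimum is to say that it will not be interpreted as a treatment effect on anxiety around the procedure.

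**Cost.** One line on an existing form and an amendment, for which Ethical aspects already gives a route. The article lists the trial as not yet recruiting, so no collected data are affected. Dropping the second GAD-7 saves about five minutes of questionnaire time per woman, by the article's own estimate. The downside is that a single item is less detailed than a full questionnaire, and the documents give no evidence on its validity; a short established state scale would reduce that drawback at the price of a few more questions.
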